**Fig 3. Study Design and Procedure**

*The upper portion indicates the overall study design. The middle portion indicates the timeline for assessment of scales and EEG at baseline and post-intervention, also follow-up time-points. Brief mindfulness and relaxation training was administered to intervention group and control group after recruitment.Baseline assessment (-T2, -T1) was finished before intervention. Audio guidance was delivered for everyday's practice for BMT group. There is no other practice and intervention for control group after training. The lower portion indicates modules of psychological and behavioral assessments during the baseline and 5 follow-up sessions. Executive function measurement was implemented via EEG tasks including Stroop, More-odd Shifting, N-back. INT: intervention, INST:monthly intensive training (red triangle); rs-EEG: resting-state EEG; BMT: brief mindfulness training; VAS: Visual analogue scale; SMT: state-mindfulness.*

1. ***Sample size estimation. [List the four elements: δ(Δ) or π1, π2, α, β or Power, and provide the calculation formula]***

In this trial, Stroop reaction time related to executive function will be used as the primary indicator, and the sample size estimation will be conducted using the pwr package in R software. It is set that δ(Δ)tot = 125, corresponding to an expected reduction of 125ms in reaction time for the experimental group after the intervention. Additionally, α is defined as 0.05 and β as 0.80.

The estimation of Cohen's d is required, with the formula Cohen's d = (δ(Δ) / SDestimate). Referencing studies in similar populations [<https://www.ncbi.nlm.nih.gov/pmc/articles/PMC8939409/>], SDestimate is taken as 250. Therefore, the relevant command is pwr.t.test (d = cohen_d, sig.level = 0.05, power = 0.80, type = "paired", alternative = "two.sided"), resulting in a sample size estimate of 34. Thus, the estimated sample size for the experimental group should be no less than 34 individuals; considering a natural dropout rate of 20%, the sample size for the experimental group should be at least 41 individuals. A ratio of 2:1 will be used to include 20 recreational gamers in the intervention group. A total of 61 participants are required for the intervention group. In order to maintain appropriate comparability, we will recruit an additional 61 participants with matching demographic profiles and equivalent levels of IGD (Internet Gaming Disorder) severity for the control group. Thus, the study demands a cumulative participation of 122 individuals in total.

1. ***Methods of randomization and concealed allocation. [Randomization is used to reduce the risk of selection bias. Methods for generating random number sequences include computer software, random number tables, semi-random or pseudo-random methods (such as using dates, birthdays, or even/odd numbers of hospital visits). Please describe the individuals involved in generating random number sequences and the methods they use. Concealed allocation is used in treatment studies to reduce the risk of selection bias. Key steps in concealed allocation include having a designated person determine the allocation sequence, ensuring that this person is not involved in enrolling participants, and securely storing the allocation table. Please provide detailed descriptions of these steps. Central randomization is a robust method of concealed allocation. Describe the individuals and methods involved in determining the allocation sequence]***

(1) In this study, the intervention period focused on breath meditation lasts for one week and serves as a concise mindfulness behavior training. The study will involve a baseline collection of EEG and other relevant data for all participants, a one-week training on the intervention content, collection of post-intervention EEG and other relevant data, and follow-ups (one week, one month, four months, six months, and one year after data collection post-intervention). During the follow-up phase, participants will undergo multiple mindfulness training sessions. Grouping will occur after the baseline data collection for participants is completed.

(2) The breath meditation training is the primary intervention method employed in this study. The design includes grouping into an experimental group and a control group: the experimental group (breath meditation training) and the control group (relaxation training). The recruited participants are from the same school, and their connections make it challenging to implement the criteria for double-blind randomization.

(3) The randomization process for this trial will utilize the random sequence generator available at random.org.

1. ***Blinding. [Blinding is used in treatment studies and diagnostic trials to reduce the risk of implementation bias and measurement bias. Implementing strict confidentiality measures, such as using placebos or simulating procedures, is an effective blinding method. If blinding is necessary and feasible for your study, describe the methods and procedures for implementing blinding]***

This trial involves group therapy, with participants being students from the same school. Therefore, it is possible that among participants who may know each other or even among those who do not, conversations related to the experimental training they are undergoing may arise. Additionally, maintaining blinding for the researchers is quite challenging, as they can easily be influenced by information related to the experiment during the process. As a result, it is not feasible to meet the double-blind requirements of clinical trials.

1. ***Outcome Measures. [Outcome measures are used to evaluate the results of a study and can include primary, secondary, and safety measures, including adverse events and reactions. Please describe the names of the measures, the methods of measurement, and the time points at which they are assessed]***

(1) Primary indicators: average daily gaming time (self-reported by participants), Five Facet Mindfulness Questionnaire (FFMQ), Internet Addiction Test (IAT), Game Craving Scale (adapted from QSU-Brief), Adolescent Executive Functioning Scale (EFS-A), Barratt Impulsiveness Scale, State Mindfulness Scale, Game Craving Visual Analogue Scale, behavioral data, and EEG data (from EEG equipment).

(2) Secondary indicators: Self-Rated Sleep Status Scale, Depression-Anxiety-Stress Scale (DASS-21), Positive and Negative Affect Schedule (PANAS).

(3) Safety indicators: Researchers will inquire daily during the intervention period whether participants experience any adverse reactions. If there are any adverse reactions, they will communicate in person or by phone with the research staff.

Measurement time points are detailed in item 5.

1. ***Definition of Participant Effectiveness Determination. [This includes definitions for participant withdrawal, exclusion, loss to follow-up, confounding factors, study discontinuation, and study suspension]***

(1) Participant Withdrawal: Each participant can withdraw from the study at any time during the experiment without providing any reason. Participants who withdraw voluntarily will not be included in the analysis. Under the conditions of a mixed study, we have a complete access procedure for withdrawn participants. If participants are willing to provide a reason for their withdrawal, it will be recorded by the researchers.

(2) Participant Exclusion: If participants cannot consistently participate in the group interventions during the training process—where the focused breathing meditation training lasts one week—those who attend fewer than 5 sessions will be considered not fully intervened and should theoretically be excluded or adjusted using a mixed-effects model.

(3) Participant Loss to Follow-up: If any participant cannot be contacted for two consecutive attempts after the intervention is completed, they will be classified as lost to follow-up.

(4) Participant Contamination: After the intervention is completed, we will conduct a census of participants. If any participant in the control group attempts to learn about the training methods of the intervention group (or vice versa) and tries to train, they will be classified as contaminated participants.

(5) Participant Termination: To ensure the health of the participants, any adverse events will constitute a termination condition. Researchers will discuss such situations with the affected participants to consider premature termination of their intervention. Appropriate clinical interventions will be provided to them with their consent.

(6) Participant Suspension: In this trial, we will allow participants to request suspension of their involvement in the intervention. If any requests for suspension are made, participants will be moved to a future intervention group after the trial team assesses that no adverse events or reactions have occurred. Data collected from these participants during the current trial will not be included in the final data analysis.

| **Table 1. Evaluated variables**   \| **Variables** \| \| **Measures** \| **Timepoints** \| \| --- \| --- \| --- \| --- \| \| **Primary outcome** \| **Trait-, State-mindfulness** \| Five Facet Mindfulness Questionnaire (FFMQ) [[6](#_ENREF_6" \o "Baer, 2006 #537)] \| -T2, -T1; T0, T1, T2, T3, T4, T5 \| \| State Mindfulness Scale [[7](#_ENREF_7" \o "Yu, 2021 #565)] \| \| **Electroencephalographic (EEG) and behavioral data** \| Behavioral and Electroencephalogram (EEG) data \| \| Heart Rate Variability \| \| **Gaming craving-related metrics** \| Average daily gaming time (self-recorded by participant) \| \| Internet Addiction Test (IAT) [[8](#_ENREF_8" \o "Wang, 2019 #706), [9](#_ENREF_9" \o "Young, 1998 #711)] \| \| Gaming Craving Visual Analogue Scale [[10](#_ENREF_10" \o "Ko, 2013 #65)] \| \| Gaming Craving Short Questionnaire (adapted from QSU-Brief) [[11](#_ENREF_11" \o "Cox, 2001 #543)] \| \| **Impulsivity** \| Barratt Impulsiveness Scale [[12](#_ENREF_12" \o "Patton, 1995 #547)] \| \| **Executive function** \| Adolescent Executive Functioning Scale (EFS-A) [[13](#_ENREF_13" \o "Huang, 2014 #707)] \| \| **Secondary outcome** \| **Sleep status** \| Self-Rating Scale of Sleep (SRSS)[[14](#_ENREF_14" \o "Li, 2012 #708)] \| -T2, -T1; T0, T1, T2, T3, T4, T5 \| \| **Affect, Stress** \| Depression Anxiety Stress Scales (DASS-21) [[15](#_ENREF_15" \o "Gong, 2010 #709)] \| \| Positive and Negative Affect Schedule (PANAS) [[16](#_ENREF_16" \o "Watson, 1988 #71)] \| \| **others** \| **Socio-demographic and clinical information** \| Demographics including name, gender, handedness [[17](#_ENREF_17" \o "Edlin, 2015 #541)], gaming history duration, average weekly gaming time, psychiatric diagnosis or history of mental health problems \| -T1 \| \| **Psychological status** \| Patient Health Questionnaire-9 (PHQ-9) [[18](#_ENREF_18" \o "Kroenke, 2001 #73)] \| \| Generalized Anxiety Disorder-7 (GAD-7) [[19](#_ENREF_19" \o "Spitzer, 2006 #544), [20](#_ENREF_20" \o "shan, 2015 #546)] \| \| **Presence of IGD** \| Diagnostic and Statistical Manual of Mental Disorders, Fifth Edition (DSM-5) nine diagnostic criteria [[21](#_ENREF_21" \o "Petry, 2014 #76)] \| \| Gaming history, average weekly gaming time \| \| **Personal traits** \| Chinese Big Five Personality Questionnaire [[22](#_ENREF_22" \o "Wang, 2011 #710)], attachment style [[23](#_ENREF_23" \o "Li, 2006 #702)], self-compassion [[24](#_ENREF_24" \o "Kong, 2021 #703)] \| |
| --- | --- | --- | --- | --- | --- | --- | --- | --- | --- | --- | --- | --- | --- | --- | --- | --- | --- | --- | --- | --- | --- | --- | --- | --- | --- | --- | --- | --- | --- | --- | --- | --- | --- | --- | --- | --- | --- | --- | --- | --- |

1. ***Definition, identification methods, and management systems for adverse events and reactions.***

[name] [[25](#_ENREF_25" \o "Farias, 2020 #701)] systematically describes the adverse events and reactions caused by meditation (meditation adverse events, MAEs) in the text, which we categorize as follows:

**Mental MAEs:** The most common include anxiety and depression, while other relatively common issues include psychotic or delusional symptoms, dissociation or depersonalization, fear or phobia, trauma re-experiencing, and suicidal thoughts and behaviors.

**Physical MAEs:** The most common is bodily tension, followed by pain and gastrointestinal issues. Localized pain often involves the abdomen/stomach and neck. Most physical MAEs are based on patient self-reports; however, some variables also used physiological and biological measurement methods, such as heart rate, blood pressure, skin conductance, and cortisol levels (it is not possible to rule out that these physiological measuring methods might cause side effects).

**Neurological/Cognitive MAEs:** The most common are abnormal cognitive experiences, including thought disorganization, forgetfulness, sensory hypersensitivity, and impaired memory reliability. Some patients also experienced involuntary bodily movements and muscle contractions during meditation.

Based on the types of adverse effects mentioned above, to address adverse events during the intervention process, we have included relevant adverse reaction feedback questions in the weekly follow-up questionnaires. The experimental group will conduct weekly monitoring; after collecting the questionnaires, if an adverse event feedback option is marked "yes," the relevant person in charge from the medical school and psychology department will be responsible for communicating with the subjects, assessing their psychological and physiological conditions, and gauging the subjects' willingness. After a tripartite consensus (medical school, psychology department, and the individual subject), they will decide whether the subjects experiencing adverse events can participate in subsequent research.

Secondly, regarding adverse reactions during the EEG data collection process, if participants show physiological rejection responses or adverse emotions, researchers will immediately cease EEG data collection. Whether to continue the experiment will depend on ensuring the participants' health and safety, as well as their own willingness to either continue participating in the experiment or withdraw, with researchers recording the reasons. Subsequent follow-ups and interventions in this study will be communicated to participants after collective discussion among the research team before any decisions are made.

1. ***Ethical considerations. [This includes the selection of an ethics committee, approval procedures, informed consent process, registration time, and registration authority (please provide registration number after completion)]***

(1) Selection of the Ethics Committee: This trial has selected the ethics committee of the implementing institution, namely the Medical Ethics Committee of Kunming University of Science and Technology.

(2) Approval Process: Before the study begins, the research project proposal and related materials have been submitted for approval in accordance with the procedural requirements of the selected ethics review committee of the research institution.

(3) Informed Consent Process: Before the study begins, researchers will provide paper copies of the informed consent form to the participants and authorized agents, and address any questions related to the informed consent form to ensure that participants and authorized agents understand the content before signing the informed consent form.

(4) Registration Time: March 2024.

(5) Registration Institution: China Clinical Trial Registration Center.

1. ***Participant recruitment. [This includes the selection of recruitment locations, recruitment methods, the screening process, and the researchers conducting the screening]***
2. Recruitment Location: Chenggong Campus, Kunming Medical University.
3. Recruitment Method: This trial will use a combination of online and offline methods to recruit participants:

Offline: Conduct presentations in classrooms, create posters, and distribute flyers;

Online: Use campus platforms such as QQ Space, WeChat Moments, and the school's community bulletin board.

1. Screening Process: Participants will be selected based on their order of participation according to inclusion and exclusion criteria.
2. Researchers Implementing Screening: Screening will be conducted by specifically trained personnel assigned to the project.
3. ***Collection of general participant information. [This includes the researchers responsible for data collection and the content of the general participant information]***

(1) Researchers Collecting Data: The specialized personnel responsible for the aforementioned participant screening.

(2) Content of General Information: Name, gender, age, grade, major, ethnicity, dominant hand, years of gaming experience, average weekly gaming duration, whether currently participating in similar trials, physical and mental health status, and other relevant information.

1. ***Baseline measures and observed variables. [For treatment studies, observed variables may not necessarily be efficacy evaluation measures, such as height and weight, but may be related to drug dosage without direct relevance to efficacy evaluation]***

(1) Baseline Indicators: Demographic information (name, student ID, gender, age, major, ethnicity, contact information, dominant hand, history of mental illness or psychiatric history, PHQ-9, GAD-7, duration of gaming, average weekly gaming time), Five Facet Mindfulness Questionnaire (FFMQ), Internet Addiction Test (IAT), DSM-5 nine diagnostic criteria, Gaming Craving Short Questionnaire, Adolescent Executive Functioning Scale (EFS-A), Barratt Impulsiveness Scale, State Mindfulness Scale, Gaming Craving Visual Analog Scale, Sleep Condition Self-Assessment Scale, behavioral data and EEG data (electroencephalography device), Depression-Anxiety-Stress Scale (DASS-21), Positive and Negative Affect Schedule (PANAS).

(2) Observation Items: Average daily gaming time, Five Facet Mindfulness Questionnaire (FFMQ), Internet Addiction Test (IAT), Gaming Craving Short Questionnaire, Adolescent Executive Functioning Scale (EFS-A), Barratt Impulsiveness Scale, State Mindfulness Scale, Gaming Craving Visual Analog Scale, Sleep Condition Self-Assessment Scale, behavioral data and EEG data (electroencephalography device), Depression-Anxiety-Stress Scale (DASS-21), Positive and Negative Affect Schedule (PANAS). The measurement tools and specific content are shown in **Table 1**. The outcome level and timepoints for assessment was annotated.

1. ***Standard operating procedures. [For treatment procedures, treatment methods, treatment courses, etc.; diagnostic trial standard procedures; etiological research standard procedures; prognosis research standard procedures; epidemiological research standard procedures]***

Trained personnel rigorously adhere to the main operating procedures related to this research process. The standard operating procedures are as follows:

(1) **Procedure for EEG data collection:**

1. Pre-collection Preparation: Inform participants of relevant precautions and prepare for the collection (including both software and hardware; software refers to the specialized computer software that links to the EEG collection device, while hardware includes the EEG cap, conductive gel, and other necessary auxiliary equipment).
2. Measure Head Circumference: Measure the participant’s head circumference to determine the appropriate size of the EEG cap (Large cap: 56-60 cm; Small cap: 54-58 cm).
3. Prepare Long Hair: If the participant has long hair, it should be tied back with a hairband before putting on the EEG cap to expose the ears (participants can prepare the hairband themselves, or it will be provided by the laboratory).
4. Correct Placement of the Cap: Place the cap on the participant’s head correctly according to the front and back of the cap and the electrode positions (the side with letters facing up, with the letter F indicating the front and O indicating the back).
5. Positioning the Cz Electrode: Measure the distance from the nasal root to the inion, and adjust the EEG cap forward and backward so that the Cz electrode is in the center of this distance. Measure the distance between the left and right ear lobes, and adjust the cap left and right to make sure the Cz electrode is at the center of this distance. The Cz electrode should be at the intersection point of the two measured distances.
6. Visual Check: Conduct a visual inspection from the front of the participant to ensure the EEG cap does not rotate or become loose. If there is looseness or incorrect electrode positioning, repeat step “e)” until the EEG cap is appropriately positioned.
7. Applying Conductive Gel: Use a specialized syringe (angled syringe) to apply conductive gel to the scalp at the corresponding channels. Since the syringe is used to part the hair, ask the participant if the pressure applied is too forceful during the process and adjust accordingly based on their feedback.
8. Insert Active Electrodes: Correspondingly insert the labeled active electrodes into the designated electrode names marked on the EEG cap (make sure to carefully match the electrodes’ labels with the EEG cap). Wrap the CMS and DRL active electrode wires around the other electrodes' cables (3-5 wraps), and plug their connectors into the corresponding matching ports on the amplifier.
9. Confirm Connections and Start Data Collection: After confirming that the EEG software and hardware are properly connected, run the software to collect EEG data. Follow the software usage instructions and ensure the quality of the EEG data meets the required standards before starting the data collection. Save the EEG data to the computer or hard drive according to your naming format.
10. Intervention Content Training Process:

The researchers of this study will collaborate with professional psychological teachers to conduct a week-long intervention content training and multiple training sessions during the follow-up phase.Before each practice session begins, participants will be reminded of the time and location of the practice, and the researchers will conduct on-site check-ins. Training for the intervention content will be provided for one week by the teachers from the Student Mental Health Education and Counseling Center, along with multiple training sessions during the follow-up phase. Professional psychological teachers will guide the training, and the content practiced each day will be sent to the participants' group after each session for continued practice.

1. ***Statistical analysis methods. [Select appropriate statistical analysis methods based on the data type of each measurement variable. Include any additional methods for subgroup analysis or auxiliary analysis. If there are personnel reductions during the trial, indicate whether an intention-to-treat (ITT) analysis was used and compare it with per-protocol (PP) analysis]***

The primary and secondary indicators of this study's scales will be presented to participants in the form of paper questionnaires, while behavioral data and EEG data will be collected from participants using electroencephalography devices.

Demographic data and scale data analysis will use SPSS software, employing t-tests, covariance analysis, etc.; EEG data analysis will utilize Matlab_2013b software, EEGLab software, and scripts.

For power spectrum and functional connectivity analysis: EEG data will calculate the relative power of six EEG frequency bands at the single electrode and ROI levels (δ: 1-4Hz, θ: 4-8Hz, α: 8-13Hz, low β: 13-20Hz, high β: 20-30Hz, low γ: 30-48Hz). Phase Locking Value (PLV) and Phase Lag Index (PLI) will be calculated using the FieldTrip toolbox. Source localization analysis will be used to explore functional changes in subcortical regions.

For ERP data, we selected the N2 and P3 components based on previous research. The analysis epoch will be 1000ms, with the baseline being the 200ms before stimulus presentation. The N2 negative component is primarily induced by the frontal central region, so the frontal midline electrodes were chosen as the region of interest. The time window for N2 is 250-350ms post-stimulus lock, while P3 is a positive component appearing in the parietal mid/post region, with the parietal electrodes selected as the region of interest, and the time window is 300-400ms post-stimulus presentation. To avoid Type I error rates, we did not analyze individual electrodes; instead, we averaged the amplitude values of the electrodes within the selected time window as the dependent variable for analysis. All work related to ERP component analysis was conducted using ERPLAB.

Finally, we will simultaneously conduct ITT analysis for this study, considering dropout levels as a very important indicator for recording and analysis, attempting to objectively reveal the intervention effects of focused breathing meditation training on executive function from both ITT and PP analysis perspectives..

1. ***Participant management system.***

(1) Contact and Guidance: A contact group composed of relevant researchers is responsible for providing guidance or answers to all research-related content or questions encountered by participants throughout the duration of the study. This ensures that participants have a sufficient understanding of the research and can better cooperate with the process. Researchers must promptly address and record any instances of withdrawal, removal, loss to follow-up, termination, or suspension involving participants.

(2) Emergency Team: Comprised of researchers and psychological teachers from the university's mental health education center, this team will timely identify and intervene in cases of adverse reactions experienced by participants during the study. In situations that cannot be resolved, they will provide additional channels for addressing the issues faced by those participants. Every participant is encouraged and expected to proactively reach out to members of this team if they encounter any health-related problems at any time.

(3) Confidentiality of Information: Any information and data obtained about participants during the study will be kept strictly confidential. Information that could identify participants will not be disclosed to anyone outside the research team without the participant's consent. Any public reports related to the results of this research will not disclose the personal identities of the participants.

1. ***Specimen management system. [This includes the processes and systems for specimen collection, storage, and submission]***

This study does not involve the collection of samples.

1. ***Drug and equipment management system. [This includes the storage and distribution processes, checking systems, use, and recovery of drugs and equipment]***

This study does not involve the use of drugs or equipment management.

1. ***Data management system. [This includes data collection, management of source data and files, personnel responsible for data collection and entry, and checking systems]***

Before statistical processing, all collected data from participants will be uniformly anonymized, and measures such as data encryption or other secure storage methods will be implemented.

(1) Data Collection: Relevant data will be collected strictly in accordance with the standard operating procedures for different data collection methods.

(2) Management of Source Data and Files: Source data will be stored on the appropriate data platform, and multiple backups of the files will be created (such as storing them on a specialized, non-networked hard drive or an external hard drive used for data analysis). For some original data stored on third-party online platforms, timely downloads and secure storage will be conducted to ensure network security, enhance endpoint protection, prevent information leakage, maintain software and data backups, and regularly check for vulnerabilities and prevent virus intrusions.

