1. ***Study design, design pattern diagram, with SPIRIT template attached. [Clearly state the design scheme used in this study, such as: consecutive case or single-arm design, cross-sectional study, case-control study, cohort study, including historical cohort study or prospective cohort study, nested case-control study, randomized controlled trial, clearly specify the type, such as parallel design, crossover design, factorial design, single-group design; for treatment studies, specify the type of research objective framework, such as superiority, equivalence, non-inferiority, exploratory]***

The current trial adopts a randomized controlled parallel design, with substantial literature supporting the moderate effect of brief mindfulness interventions on executive function [[5](#_ENREF_5" \o "Zhou, 2020 #694)]. Therefore, for the IGD population, this trial aims to demonstrate superiority under the condition of a brief mindfulness intervention compared to the control group. The trial comprises four stages: participant recruitment, baseline assessment, post-intervention measurement, and follow-up assessment, with corresponding evaluations conducted at the conclusion of each phase. A schematic diagram of the design is depicted in **Fig 3.** The trial has not yet commenced, and it is estimated that the entire process from initiating participant recruitment to completing data analysis and manuscript writing will take approximately one year.

**
[figure not shown]
**

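### The 80% power belongs to a paired pre-post test within the mindfulness arm, not to the stated aim of superiority over the relaxation control in IGD participants

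*Protocol*

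**What the plan says.** The study design section of the protocol describes parallel randomised groups ("The current trial adopts a randomized controlled parallel design") and sets the aim: "for the IGD population, this trial aims to demonstrate superiority under the condition of a brief mindfulness intervention compared to the control group". The randomisation section identifies the control as relaxation training.

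The sample size section takes Stroop reaction time as the sizing endpoint ("Stroop reaction time related to executive function will be used as the primary indicator"). The effect is 125 ms, "corresponding to an expected reduction of 125ms in reaction time for the experimental group after the intervention". The standard deviation is given without saying of what: "SDestimate is taken as 250". The standardised effect is "Cohen's d = (δ(Δ) / SDestimate", that is 125/250 = 0.5. The test is paired: "type = 'paired', alternative = 'two.sided'), resulting in a sample size estimate of 34". The 34 becomes 41 for 20% dropout, and 20 recreational gamers bring the mindfulness arm to 61. A control group of 61, matched on demographics and IGD severity, is then added, for 122 in all. No between-arm difference, no expected change under relaxation and no pre-post correlation appears.

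The statistical methods section lists t-tests and covariance analysis among the methods and does not name the test for the primary comparison.

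**The concern.** A paired test within one arm asks whether mindfulness participants change from their own baseline. A superiority trial asks whether they change more than participants given relaxation. The second question carries sampling error from two arms, and its effect is the within-arm fall minus whatever fall occurs in the control arm. The calculation allows for neither.

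Two things are at stake. Readers are told of 80% power that was never calculated for the randomised comparison. And if the between-arm power is well below 80%, a null result could be read as absence of effect when the trial had a limited chance of detecting the effect it assumed.

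**Working it through.** **Inputs, all from the sample size section:** difference 125 ms; SD 250 ms; d = 125/250 = 0.5; two-sided α = 0.05; power 0.80; dropout 20%. The text has "α is defined as 0.05 and β as 0.80"; the 0.80 is evidently the power, as the command shows.

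**1. The plan's own figure.** Paired t-test, noncentral t, d = 0.5, α = 0.05, power 0.80: n = 33.37, so 34. Reproduced. The 41 is 34 × 1.2 = 40.8, rounded up. Losing 20% of 41 leaves 41 × 0.8 = 32.8, about 33.

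**2. The same d for two independent groups.** Power comes from the noncentral t with noncentrality d × √(n/2) and 2n − 2 degrees of freedom, n per arm. Reaching 80% needs n = 63.77, so 64 evaluable per arm. At the planned numbers:

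| Analysis set | n per arm | Power |
|---|---|---|
| IGD only, no loss | 41 | 60.9% |
| IGD only, 20% lost | 33 | 51.6% |
| IGD and recreational gamers pooled, no loss | 61 | 78.2% |
| Pooled, 20% lost (61 × 0.8 = 48.8) | 49 | 68.8% |

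This treats the whole 125 ms as the between-arm difference, so it assumes no change under relaxation. It also assumes 41 IGD participants in the control arm.

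**3. If the control arm improves too.** With a between-arm difference of 100 ms (an assumption, for illustration), d = 100/250 = 0.4 and power is 43% at 41 per arm and 36% at 33.

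**4. Adjusting for baseline.** Let r be the correlation between the baseline mean and T0. ANCOVA power uses the residual SD in place of 250, with 2n − 3 degrees of freedom. The residual SD depends on what 250 is:

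- If 250 is the SD of raw reaction time, residual SD = 250 × √(1 − r²): 216.5, 200.0 and 178.5 for r = 0.5, 0.6 and 0.7.
- If 250 is the SD of change, as a paired d requires, and variances are equal at baseline and T0, the raw SD is 250/√(2(1 − r)). The residual SD is then 250 × √((1 + r)/2): 216.5, 223.6 and 230.5.

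Power for a 125 ms between-arm difference:

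| Reading of 250 | n per arm | r = 0.5 | r = 0.6 | r = 0.7 |
|---|---|---|---|---|
| SD of raw RT | 33 | 64% | 71% | 80% |
| SD of raw RT | 41 | 73% | 80% | 88% |
| SD of change | 33 | 64% | 61% | 58% |
| SD of change | 41 | 73% | 71% | 68% |

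The values of r are assumptions; the protocol gives none. The two readings agree at r = 0.5 and move in opposite directions above it.

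**The case against.** The strongest reply is that the protocol does not commit to an unadjusted t-test. Covariance analysis is among its listed methods, and a mixed-effects model is mentioned in the section on participant exclusion. The primary test may be fixed in a statistical analysis plan that is not available here. With adjustment, the existing numbers could reach 80%. This stands in part: a reader might infer that the trial simply has 52% to 61% power, and the documents do not support that as an unconditional statement. But 80% is reached only if 250 is the raw SD and r is about 0.7 at 33 per arm or 0.6 at 41. The protocol states neither. Under the reading that its own paired formula requires, none of the values of r examined reaches 80%.

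A second reply is that the recreational gamers could be pooled with the IGD participants. The superiority aim is limited to the IGD population, and pooling still gives only 78% before dropout and 69% after it in an unadjusted test.

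A third is that the 41 IGD controls are nowhere written. That is correct. The number follows from matching the control arm on size and IGD severity, and the percentages for IGD participants depend on it. The mismatch between test and aim does not.

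A reader might also infer that the trial will claim efficacy from a significant pre-post change in the mindfulness arm, which practice on the Stroop task could produce. The paired test appears only in the sample size command; the statistical methods section names no within-arm efficacy test. Nor does the protocol say how the 125 ms was derived, so it cannot be shown how much practice, if any, it contains.

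**Conclusion.** The concern holds as a mismatch between aim and calculation, not as an arithmetic slip: 34 is right for the test used, and the test used is not the trial's question. The stated 80% power does not apply to superiority over relaxation in IGD participants.

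The shortfall is conditional. The figures of 61% (41 per arm) and 52% (33 per arm) rest on an unadjusted two-sample t-test, or one on change scores with 250 as the SD of change. They also assume the full 125 ms as the between-arm difference and an equal IGD split between arms. A smaller difference gives less power. ANCOVA gives between 58% and 88% over the range shown, depending on r, on the meaning of 250 and on dropout. The size of the shortfall therefore cannot be fixed from the protocol, but the 80% cannot stand as written.

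**What to change.** In the sample size section:

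- Replace the paired calculation with the between-arm comparison in the IGD stratum at T0, analysed by ANCOVA on Stroop reaction time with the mean of the two baselines (-T2 and -T1) as covariate.
- State the assumed between-arm difference separately from the expected fall within the mindfulness arm, allowing for any change expected under relaxation.
- Say whether 250 is the SD of raw reaction time or of change, and give the assumed correlation between the baseline mean and T0.
- Write down the number of IGD participants in each arm.
- Restate the power at the existing size under the correct reading, before and after 20% dropout.

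The cost is a rewritten paragraph and probably a stated power below 80%. Both baselines are already scheduled and this correction needs no extra participants. It discloses any shortfall rather than removing it. The study design section says that the trial has not started, so the change can be made before recruitment.
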